### Sample size

This study aims to compare the microbial community structure between the ASD and TD healthy groups and within the groups, generating plausible distances relevant to the study objectives. Beta diversity is used to estimate the sample size or statistical power for this study. The recommended sample size is 60 participants, determined based on calculations using data from a study conducted by Li et al. [31]. Due to the limited availability of similar studies, this prior research served as a reference to obtain appropriate variance estimates [31]. The total study sample size of 60 participants has been adjusted to account for a possible 30% dropout rate; thus, this study aims to recruit 80 participants (40 children with ASD and 40 TD healthy children). The primary outcomes are microbial beta diversity and nutritional status. Secondary microbiota comparisons will be adjusted for multiple testing using the Benjamini-Hochberg false discovery rate, and post-hoc power analyses will be conducted to assess adequacy for multivariate models.

The study included only male children to eliminate potential gender bias, as the male predominance in ASD has been well-documented in epidemiological studies and widely recognised in the field [32–34]. This approach also ensures greater homogeneity in the demographic and microbiome datasets, thereby enhancing the precision and reliability of the findings.

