DNA will be extracted using Zymo Quick-DNA MagBead Plus Kit. The purity of the extracted DNA samples will be assessed using Implen NanoQuant Spectrophotometer, and DNA libraries will be prepared using the DNA library Prep (Illumina, CA, USA) according to the manufacturer’s instructions. The prepared DNA libraries will be sequenced on Illumina Novaseq 6000 system (Illumina, CA, USA) at PE150. Libraries will be normalised to 1.75nM and pooled before loading into the NovaSeq sequencing platform. Demultiplexing of samples will be performed using Illumina DRAGEN BioIT Platform (Illumina) v3.9. CCMetagen pipeline will be used for taxonomic identification. Raw sequence reads (FASTQ files) will be trimmed and analysed using One Codex (https://www.onecodex.com/) to assess alpha diversity (as measured by the Shannon index) and to identify relative microbial abundances within the oral and gut microbiome of each participant.

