### Statistical analysis plan

Data analysis will be conducted using R software and its available packages. The differences in microbiota profiles, socio-demographic factors, emotional and eating behaviour, and nutritional status between children with ASD and TD children will be compared using the chi-square/Fisher’s exact test and ANOVA where appropriate. Student’s t-test will be applied to compare BMI and age between groups. Pre-filtering and inference of correlations will be performed using the Sparse Correlations for Compositional Data (SparCC) correlation metric [66], with a minimum R-value threshold of 0.35. SparCC will be used to correlate salivary and faecal bacterial markers detected in saliva and faecal samples from the same child. The associations between microbiota profiles, socio-demographic factors, emotional and eating behaviour, autism severity, sleep quality, gastrointestinal symptoms, and nutritional status among children with ASD will be modelled using mixed-effects logistic regression (MELR) model and random forest. Normality, linearity, homoscedasticity, and multi-collinearity will be assessed to ensure that the assumptions of regression models are met. Potential confounders, including age, and socioeconomic status will be adjusted for fixed effects. Model assumptions will be performed using DHARMa package in R to assess dispersion, zero-inflation and overall fit [67]. In case of heteroscedasticity or overdispersion, corrective strategies will include the use of an observation-level random effect, modelling dispersion or zero-inflation with glmmTMB [68], or applying bias-reduced logistic regression (Firth correction) [69] or bootstrap inference to mitigate small-sample bias [70]. Study results are expected in December 2026.

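### SparCC with a fixed R of 0.35 is the stated inference rule for saliva–stool correlations; it treats two separate compositions as one and does not control error

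*Protocol article*

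**What the plan says.** The Statistical analysis plan section gives one method for the whole step: "Pre-filtering and inference of correlations will be performed using the Sparse Correlations for Compositional Data (SparCC) correlation metric", "with a minimum R-value threshold of 0.35". The next sentence says what it is applied to: "SparCC will be used to correlate salivary and faecal bacterial markers detected in saliva and faecal samples from the same child". The section attaches no p-value, bootstrap, permutation or false discovery rule to these correlations. It does not say whether they are computed over all children or by group, or whether the cut-off applies to R or to its absolute value.

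The data are proportions within each site. The sample collection and analysis section plans "to identify relative microbial abundances within the oral and gut microbiome of each participant", from saliva and stool collected and sequenced as separate samples.

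The Sample size section gives two sample sizes: "The recommended sample size is 60 participants", and after inflation "this study aims to recruit 80 participants (40 children with ASD and 40 TD healthy children". It also contains the only multiplicity rule: "Secondary microbiota comparisons will be adjusted for multiple testing using the Benjamini-Hochberg false discovery rate". Correlations are not named there.

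**The concern.** SparCC works from variances of log-ratios between taxa. Within one sample the unknown total is in both numerator and denominator and cancels. In a ratio of a saliva taxon to a stool taxon it does not, because each site is closed to its own total. The method is therefore assigned to a comparison for which its main assumption fails.

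Separately, a minimum R is a statement about effect size. Used as the inference rule, it has an error rate that changes with the number of children, and the number of chance links grows with the number of taxon pairs. The plan fixes neither.

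At stake is the credibility of any oral–gut links that are reported. The Discussion hopes that bacterial markers associated with ASD will help to stratify patients, so links that arise by chance or from the method could be carried forward.

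**Working it through.** **The plan's own figure.** The 0.35 comes with no alpha, n, number of taxa or derivation, so there is nothing to reproduce. What can be computed is the error rate it implies.

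**Inputs.** Cut-off 0.35 (Statistical analysis plan). Sample sizes 80 and 60 (Sample size), or 40 and 30 per group, the last assuming an equal split of 60. Taxa per site are not given; 50 and 100 are assumptions.

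**Chance rate per unrelated pair.** As an approximation to a null correlation, t = r·√((n−2)/(1−r²)), two-sided on n−2 degrees of freedom. With r = 0.35, 1−r² = 0.8775.

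- n=30: t = 0.35·√(28/0.8775) = 1.98, p = 0.058
- n=40: t = 0.35·√(38/0.8775) = 2.30, p = 0.027
- n=60: t = 0.35·√(58/0.8775) = 2.85, p = 0.0061
- n=80: t = 0.35·√(78/0.8775) = 3.30, p = 0.0015

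Expected chance links, if no pair is truly related, are p × (saliva taxa × stool taxa).

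| n | r needed for unadjusted 5% | p at 0.35 | 50 x 50 (2,500 pairs) | 100 x 100 (10,000 pairs) |
|---|---|---|---|---|
| 30 | 0.361 | 0.058 | 145 | 580 |
| 40 | 0.312 | 0.027 | 67 | 268 |
| 60 | 0.254 | 0.0061 | 15 | 61 |
| 80 | 0.220 | 0.0015 | 4 | 15 |

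At n=30 the cut-off is looser than a single unadjusted test. Between n=80 and n=30 the error rate rises about 40-fold (0.05796/0.00146). If only positive R counts, every rate and count halves. For comparison, a Bonferroni 5% limit over 10,000 pairs would need |r| of about 0.73, 0.65, 0.55 and 0.49 at n = 30, 40, 60 and 80.

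**SparCC across two sites.** Let saliva taxon x have site total T_A and stool taxon y have site total T_B. Then log(x/T_A) − log(y/T_B) = (log x − log y) − (log T_A − log T_B), so the variance of the ratio carries the variation of both totals. Within a site that term is absent. SparCC also assumes that correlations are small on average. The shared total raises correlations within each site, and cross-site values are pushed down to balance.

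The size was checked by coding basic SparCC and running it on independent saliva and stool compositions joined into one table. All settings are assumed: 50 taxa per site, log-SD 1, 60 runs per scenario. The dominant taxon, where present, had a log-mean 3 above the largest other taxon and a log-SD of 2. The cells show the share of unrelated cross-site pairs with |r| ≥ 0.35.

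| n | SparCC, no dominant taxon | SparCC, one dominant variable taxon per site | Each site log-ratio transformed separately |
|---|---|---|---|
| 30 | 6.1% | 71% | 5.8–5.9% |
| 40 | 3.1% | 70% | 2.7% |
| 60 | 0.93% | 78% | 0.6% |
| 80 | 0.24% | 81% | 0.17% |

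The mean cross-site r was about −0.03 without the dominant taxon and −0.40 to −0.42 with it, at every n. The mean within-site r was +0.03 and +0.41 to +0.43. Other assumed degrees of dominance gave 1.2% and 1.8% at n=80, about 8 and 12 times the nominal 0.15%. The size therefore depends strongly on the assumed abundance structure.

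**The case against.** The strongest reply is that this is one paragraph of a condensed article. A minimum R is a floor, the text does not call it the only criterion, and a test could be described in a fuller document. The Sample size section does promise Benjamini-Hochberg control. This stands in part: it cannot be concluded that no test will be run. But the article names the SparCC step as inference and gives only the cut-off. A false discovery rule needs p-values, none is named for these correlations, and no such rule would repair the use of SparCC across two sites.

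A second reply is that the chance-link count is small for a pooled analysis. This stands: at n=80 with 50 x 50 taxa it is about 4 of 2,500, and with 20 x 20 it is 0.6. The larger counts need analysis by group or many taxa, and the article settles neither.

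A third is that the simulated bias needs a joined table and a dominant taxon, neither of which the article describes. This also stands. Without a dominant taxon the rates are near nominal. If only positive R is retained, the negative artefacts would not be listed as links, although they would still pull true positive correlations down.

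A reader might infer that most reported links would be chance, or that ASD-versus-TD differences between networks would be noise. The documents support neither. The share of false links cannot be judged without knowing how many true ones exist, and no comparison of networks between groups is announced.

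**Conclusion.** The point holds in a limited form. The article fixes a method whose assumption of one shared total fails for saliva–stool pairs, and a cut-off that does not control error at any stated level.

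The chance rate per unrelated pair runs from 0.15% (n=80) to 5.8% (n=30). The link counts rest on assumed taxa numbers, on reading the cut-off as |R|, and on an all-null setting. The cross-site bias follows from the method. Its size, from near nominal to most pairs passing, rests on the assumed dominance and on joining the sites into one table.

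The primary outcomes, beta diversity and nutritional status, do not depend on this step. The change should be made before analysis, but the point does not threaten the main comparison.

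**What to change.** Replace the saliva–stool rule as follows.

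- Filter taxa by prevalence and abundance, not by the correlation itself.
- Apply the centred log-ratio transform to saliva and stool separately.
- Compute cross-site rank correlations, with permutation p-values from shuffling children within group.
- Declare links at a 5% Benjamini-Hochberg false discovery rate, and extend the sentence under Sample size to name these correlations.
- Keep 0.35 only as a display or effect-size floor, and state whether it means R or |R|.
- Reserve SparCC for correlations within one site.
- State whether the analysis is pooled or by group.

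Other methods for two separate compositions would also serve. The cost is a little more analysis code, revised wording and fewer reported links, especially if the analysis is by group. No new data are needed.

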**Methods and analysis:**

This observational, age-matched, case-control study is conducted in Malaysia among 40 male children with ASD and age-matched with 40 TD healthy controls aged 4–10 years. The dependent variables include the microbiota profile, identified through metagenomic sequencing analysis of saliva and faecal samples, and autism severity, assessed through validated questionnaires. Independent variables include nutritional status, determined through Subjective Global Nutrition Assessment (SGNA), anthropometry and dietary measurements, gastrointestinal symptoms, eating behaviour, behavioural profile, and sleep quality. Data collection is expected to be completed by June 2026. The study nature may limit causality establishment. Analyses will use chi-square/ANOVA for group comparisons, SparCC for microbiota correlations, and mixed-effects logistic regression to model associations.

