### Objectives

This study primarily aims to understand the role of oral and gut microbiota in the molecular mechanisms underlying the aetiology of ASD among children in Malaysia. Specifically, this study aims to determine whether there is an association between the oral and gut microbiota and socio-demographic factors, nutritional status, and autism severity among children with ASD compared to TD healthy children. Additionally, this study also measures additional independent variables to determine the associations between oral and gut microbiota and gastrointestinal symptoms, eating behaviour, behavioural profiles and sleep quality.

The hypothesized relationships between gut microbiota, nutritional status, dietary intake, and ASD severity are illustrated in Fig 1.

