Furthermore, the Autism Treatment Evaluation Checklist (ATEC) is an instrument designed to quantitatively assess the effectiveness of treatments for children with ASD [58]. ATEC composes 77 items distributed across four subscales: 1) speech/language/communication, 2) sociability, 3) sensory/cognitive awareness, and 4) health/physical behaviour. The sum of the scores for each subscale gives the total ATEC score ranging from 0 to 179. For the interest of this study, only the first subscale, speech/language/communication (14 items) will be utilized to assess the language ability of children with ASD, with scores for this section ranging from 0 to 28. A lower total score indicates less severe symptoms of ASD, while a higher total score correlates with more severe symptoms of ASD. The internal reliability of ATEC is very high, with a total score reliability of 0.94, based on a split-half reliability test conducted on over 1,300 completed ATECs [59]. The results also showed good content validity and internal consistency (Cronbach’s alpha: 0.86–0.93) [59].

The Autism Quotient-Child (AQ) is a 50-item parent-report questionnaire using a Likert scale to assess autistic traits in children aged 4–11 years [60]. Parents will be asked to rate the extent to which they agree or disagree with statements about their child, using the following answer categories: 0 representing definitely agree; 1 slightly agree; 2 slightly disagree; and 3 definitely disagree. The Likert response format helps parents assess their children’s difficulty level, which is useful for screening for ASD and determining the severity of symptoms. The scale includes reverse items (1, 3, 8, 10,11, 14). Overall, the score range is from 0–150, with higher scores (76 and above) suggesting the presence of ASD traits. The sum of each item score represents the total AQ score, where a minimum AQ score of 0 indicates no autistic traits, and a maximum score of 150 suggests full endorsement of all autistic traits. The AQ-Child has been translated into multiple languages, with the Malay AQ-Child version demonstrating good reliability and validity with a Cronbach’s alpha value of 0.82 [61].

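### The association model is mixed-effects logistic regression, but the named outcomes are not binary and no binary endpoint or grouping factor is tied to it

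*Protocol article*

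**What the plan says.** All references are to the protocol article.

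- **Model and population.** Under Statistical analysis plan, associations between microbiota, socio-demographic factors, behaviour, autism severity, sleep, gastrointestinal symptoms and nutritional status "among children with ASD will be modelled using mixed-effects logistic regression (MELR) model and random forest". The Abstract repeats the choice: "mixed-effects logistic regression to model associations". No other parametric association model is named.
- **Outcomes.** The Abstract states: "The dependent variables include the microbiota profile, identified through metagenomic sequencing analysis of saliva and faecal samples, and autism severity".
- **Scale of the microbiota outcome.** Under Saliva and stool sample collection and analysis, sequencing is used "to assess alpha diversity (as measured by the Shannon index) and to identify relative microbial abundances".
- **Scale of severity.** Under Parent report questionnaires, the ATEC language subscale runs from 0 to 28. For the AQ: "Overall, the score range is from 0–150, with higher scores (76 and above) suggesting the presence of ASD traits".
- **Checks and remedies.** Statistical analysis plan lists normality and homoscedasticity among the assumptions to be checked. If dispersion is a problem, "corrective strategies will include the use of an observation-level random effect", alongside glmmTMB, Firth correction and the bootstrap.
- **Objective.** Objectives asks about associations of the microbiota with socio-demographic factors, "nutritional status, and autism severity among children with ASD compared to TD healthy children". The secondary aim in the Abstract concerns the ASD group only.
- **Adequacy.** Under Sample size, "post-hoc power analyses will be conducted to assess adequacy for multivariate models".

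**The concern.** Logistic regression needs a binary outcome, or a count of successes out of a known total. The two severity scores are neither, and the Shannon index and relative abundances are continuous or compositional. An analyst who follows the text must therefore choose a cut-point that the article does not give. The one severity cut-off available, AQ 76, marks the presence of autistic traits. Every child in this model already has a DSM-5 diagnosis, so that cut would probably vary little among them. The normality and homoscedasticity checks belong to a linear model, which suggests that the section does not settle which model is meant.

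The word mixed-effects raises a second problem, because no grouping factor is named. Severity and nutritional status are described as single assessments. Restricting the model to ASD also leaves one child per matched pair. For such outcomes each child supplies one row, and with a binary outcome there is nothing from which to estimate a random intercept. The observation-level random effect offered as a remedy has the same defect.

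At stake are the severity and nutrition associations. They could depend on a cut-point chosen after the data are seen and on a variance that the data do not determine.

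**Working it through.** **1. Number of children.** The plan inflates 60 for 30% dropout to reach 80. 60 × 1.30 = 78, close to the stated 80 (60 / 0.70 gives 86, which is a separate question). Half of 80 is 40 ASD children. If 30% are lost, 40 × 0.70 = 28. The range used below is therefore 28 to 40.

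**2. Outcome against model.**

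| Outcome | Measured as | Binary form tied to the model? |
|---|---|---|
| Autism severity (AQ) | 0–150 | No; 76 is a cut for presence of traits |
| Autism severity (ATEC language) | 0–28 | No |
| Microbiota | Shannon index, relative abundances | No |
| Nutritional status (a primary outcome under Sample size) | SGNA class, z-scores, nutrient adequacy | Classes exist, none is tied to the model |

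**3. The AQ cut-off.** The article does not say how many diagnosed children score below 76. As an assumption, if 0 to 15% do, the rarer class has 0 to 4.2 of 28 children (0.15 × 28) or 0 to 6 of 40 (0.15 × 40).

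**4. Random intercept with one binary outcome per child.** The likelihood depends on the data only through the marginal probability P(Y=1) = ∫ expit(b0 + b1·x + σu) φ(u) du.

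- *No covariate, 20 events in 40 children (simulated).* For every σ there is a b0 that gives a probability of 0.5. The maximum log-likelihood is 40 × ln 0.5 = −27.7259 at σ = 0, 1, 2 and 4. The variance is not identified.
- *One standard normal covariate, 40 children (one simulated data set, true slope 1).* Only the slight difference in curve shape carries information on σ:

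| σ | Max log-likelihood | Slope | Odds ratio, exp(slope) |
|---|---|---|---|
| 0 | −23.9078 | 1.327 | 3.8 |
| 1 | −23.9003 | 1.585 | 4.9 |
| 2 | −23.8938 | 2.149 | 8.6 |
| 4 | −23.8907 | 3.559 | 35 |

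The log-likelihood changes by 23.9078 − 23.8907 = 0.0171 over the whole range. The data cannot choose between these odds ratios. An observation-level random effect on ungrouped binary data is the same model, so the result is the same.

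**5. Illustrative cost of dichotomising.** Assumptions, none from the article: two-sided alpha 0.05, power 80%, a normal score, a median split.

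- Continuous score: r = tanh[(1.960 + 0.842) / √(n − 3)]. This gives 0.431 at n = 40 and 0.508 at n = 28.
- Median split: divide by √(2/π) = 0.798. This gives 0.540 and 0.637. The effective n is n × 2/π, or 25.5 and 17.8.
- Power at r = 0.45 falls from 84% to 63% at n = 40, and from 68% to 47% at n = 28.

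**6. Events per predictor.** With seven predictors (an assumption) and an even split: 14/7 = 2.0 at n = 28 and 20/7 = 2.9 at n = 40. If the outcome has 30% prevalence: 8.4/7 = 1.2 and 12/7 = 1.7.

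**The case against.** The best defence is that an article condenses its analysis plan. It need not list every outcome coding, and logistic regression has legitimate uses here. SGNA class, nutrient adequacy, growth classes, the high/low gastrointestinal score and SDQ bands could all be made binary. Random forest, also named, accepts continuous outcomes. Firth correction and the bootstrap already address small-sample bias. This stands for outcomes that are truly binary. It does not rescue the AQ and ATEC scores, since the article names both the model and the dependent variables and the two do not fit. Random forest gives no adjusted effect estimate to take the regression's place.

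Several stronger readings are tempting but go beyond the documents:

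- **That no random effect can ever be estimated.** Each child gives two saliva and two stool samples. If several samples enter the model with microbiota as outcome, a child intercept can be supported. If reads for a taxon out of total reads are modelled, overdispersion is real and an observation-level effect is estimable. The article does not exclude either.
- **That the plan cannot compare ASD with TD children.** Statistical analysis plan gives group differences their own tests (chi-square or Fisher, ANOVA, t-test), and the ASD-only model matches the Abstract's secondary aim. What remains is narrower. Objectives can be read as asking whether associations differ between groups; those tests compare levels, and the ASD-only model contains no TD children.
- **That a median split is planned, or that every subscale enters one model.** Neither is stated. The figures in steps 5 and 6 of the working are illustrations.
- **That the post-hoc power will merely restate the p-value.** That is so if it uses the observed effects, but the article does not say which effects it will use.

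**Conclusion.** The point holds in a limited form. The only parametric association model named does not match the scale of the named dependent variables, and no binary endpoint or grouping factor is tied to it. For a binary outcome measured once per child in the ASD group, neither a random intercept nor an observation-level random effect can be estimated. In the example the odds ratio ran from 3.8 to 35 at practically equal fit; that range comes from one simulated data set and shows the mechanism, not the expected error in this study. The loss from dichotomising (detectable r of 0.43 to 0.54 at 40 children, 0.51 to 0.64 at 28) depends on the assumed median split.

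The point concerns association modelling. It does not touch the sample size, which rests on beta diversity, or the separate ASD-versus-TD tests. It does not extend to microbiota outcomes with repeated samples per child or grouped counts.

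**What to change.** Change the Abstract and Statistical analysis plan as follows.

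1. Analyse AQ and ATEC language scores as continuous, by linear regression with robust or bootstrap standard errors, adjusted for age and socioeconomic status.
2. For microbiota outcomes, name a model suited to continuous or compositional data. Include a child random intercept only where several samples per child enter the model.
3. Keep logistic regression, with Firth correction if events are sparse, for outcomes that are truly binary, and name those outcomes and their cut-points. Drop the observation-level random effect for ungrouped binary data.
4. Reconcile Objectives with the ASD-only model. Either state the association aim for ASD children alone, as the Abstract's secondary aim does, or add TD children and a group-by-predictor term. The second option is open only for variables measured in both groups; ATEC language and the CSHQ are described for children with ASD.
5. Under Sample size, replace post-hoc power with confidence intervals for the multivariable models.

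The cost is a little more analysis work and fewer predictors per model. No data collection changes. Recruitment is expected to end in June 2026 and results are due in December 2026. The wording should be settled before outcome data are examined, so that the choice of model and cut-points is not driven by the data.

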This study aims to address the knowledge gap by exploring the potential association between microbiota profiles, nutritional status and autism severity in children with ASD. Previous research has highlighted the potential role of gut microbiota imbalances, nutritional deficiencies, and their contribution to ASD progression [10,12–14,18,19,26–29]. However, there remains a lack of understanding of these relationships in Southeast Asia, particularly in Malaysia, where cultural and dietary practices may influence these factors differently from Western populations. This research is among the first comprehensive studies in Malaysia to simultaneously examine microbiota profile alongside nutritional status, particularly BMI and ASD severity. Existing studies have not fully integrated these components, often focusing solely on microbial diversity or gastrointestinal symptoms. The inclusion of nutritional status and a thorough analysis of dietary factors influenced by Malaysian culture are strengths of this study. The main strength of this research is its case-control study design, enabling the identification of specific microbiota and nutritional patterns associated with ASD severity as compared to TD healthy controls. By providing baseline data specific to the Malaysian context, this research aims to address the limited studies on the nutritional and microbiome profiles of children with ASD in Southeast Asia. With additional independent variables such as eating behaviour, behavioural profile, and sleep quality, the findings from this study could guide the development of targeted interventions, such as dietary modification or medical management, tailored to the unique needs of Malaysian children with ASD, ultimately enhancing their health and well-being.

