### Study Population and setting

Male children between 4–10 years old who comply with the protocol definition and inclusion criteria will be enrolled as participants. Cases are defined as male children diagnosed with ASD and receiving under follow-up care at the Paediatric Clinic at HTJ. Controls are defined as age-matched, TD healthy male children from daycare centres near IMU Healthcare and TABIKA KEMAS in Seremban. These locations were selected based on convenience sampling. Cases and controls are matched within using an age range of ±6 months.

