### Data collection sheet

This sheet contains two sections as follows: (1) Information on participant and family demographics (child’s gender, age, gestational age, birth weight, parent’s age, ethnicity, occupation, education level, and household income); and (2) ASD medical history (age of first presentation, first presenting complaint, family history of ASD or other neurodevelopmental disorders (NDDs)) and other relevant medical conditions, if applicable.

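### The ASD-versus-TD comparisons are planned without covariates; as written, the adjustment for socioeconomic status reaches only the regression among children with ASD

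*Protocol article*

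**What the plan says.** The Statistical analysis plan section of the protocol article separates two kinds of analysis.

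- **Between groups.** Differences in microbiota, socio-demographic factors, behaviour and nutritional status "between children with ASD and TD children will be compared using the chi-square/Fisher’s exact test and ANOVA where appropriate". In addition, "Student’s t-test will be applied to compare BMI and age between groups". No covariate is named for any of these.
- **Within cases.** Associations "among children with ASD will be modelled using mixed-effects logistic regression (MELR) model and random forest". After the model-assumption sentence comes the only statement on adjustment: "Potential confounders, including age, and socioeconomic status will be adjusted for fixed effects".

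The Abstract makes the same split: chi-square/ANOVA for the group comparisons and mixed-effects logistic regression for the associations.

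On recruitment, Study Population and setting takes cases from the paediatric clinic at HTJ, and controls from daycare centres near IMU Healthcare and from TABIKA KEMAS in Seremban. It adds: "These locations were selected based on convenience sampling". Matching is on age, within 6 months. The study is restricted to boys, and recent use of listed medications is excluded in both groups. The Data collection sheet records "ethnicity, occupation, education level, and household income". The Sample size section names beta diversity and nutritional status as primary outcomes.

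**The concern.** The study's main contrast is ASD against TD, and its two groups are recruited through different channels. A hospital follow-up clinic and a set of conveniently chosen childcare sites can differ in household income, education and ethnic mix. The design controls age, sex and recent medication. It does not control SES, although the plan recognises SES as a potential confounder and collects the data to address it.

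If SES differs between the groups and also predicts microbiota or nutritional status, the unadjusted tests will attribute part of that difference to ASD. An SES term in a model fitted to cases alone does nothing about this, because that model contains no case-control contrast. Recruiting more children does not help either: the bias stays the same while the test becomes more likely to detect it.

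**Working it through.** **Step 1: which analysis carries the adjustment.** The documents give no figure to reproduce here, so the text is set side by side.

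| Analysis | Children | Method named | Covariates named |
|---|---|---|---|
| Group differences | ASD and TD | chi-square/Fisher, ANOVA, t-test | none |
| Associations | ASD | mixed-effects logistic regression, random forest | age and SES as fixed effects |

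Fixed effects are terms of a regression model; a chi-square test or t-test has none. The only regression described is the one in the second row. The adjustment sentence follows that model and its assumption checks. So, as written, the adjustment does not reach the first row.

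**Step 2: what the design already controls.** Age is controlled by matching, sex by restriction and recent medication by exclusion. SES and ethnicity are neither matched nor restricted. The tests, as worded, are also unpaired and make no use of the age matching.

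**Step 3: how large the effect could be.** The documents give neither an SES imbalance nor an SES-outcome correlation, so both are assumptions.

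- Group sizes: n = 40 per group (the recruitment target of 80) and n = 30 per group (the 60 before the dropout allowance).
- d = SES difference between groups in SD units; r = within-group correlation of SES with a continuous outcome of SD 1; no true ASD effect.
- Bias = d × r. Noncentrality = d × r / √(2/n). The rejection rate is taken from the noncentral t with 2n − 2 degrees of freedom, two-sided 5%.

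Worked example, n = 40, d = 0.8, r = 0.5: bias = 0.8 × 0.5 = 0.40 SD; noncentrality = 0.40 / √(2/40) = 0.40 / 0.2236 = 1.79; with 78 degrees of freedom the rejection rate is 42%.

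| d | r | Bias (SD) | Unadjusted, n = 30 | Unadjusted, n = 40 |
|---|---|---|---|---|
| 0.3 | 0.2 | 0.06 | 5.6% | 5.8% |
| 0.5 | 0.3 | 0.15 | 8.8% | 10.2% |
| 0.8 | 0.3 | 0.24 | 15.0% | 18.5% |
| 0.5 | 0.5 | 0.25 | 15.9% | 19.7% |
| 0.8 | 0.5 | 0.40 | 33.2% | 42.4% |
| 1.0 | 0.4 | 0.40 | 33.2% | 42.4% |

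With SES as a covariate, simulation (2,000 runs per setting, d from 0.3 to 0.8, r from 0.2 to 0.5) gave 4.0% to 5.8%, which is 5% within simulation error. The rate depends on d and r only through their product. Pairing both extremes (d = 1.0, r = 0.5, bias 0.50 SD) would go beyond the table, to about 60% at 40 per group.

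**The case against.** Several points on the other side have force.

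- **The restriction to cases is inferred.** The adjustment sentence does not itself say that it applies only to children with ASD. The assumption sentence before it speaks of regression models in the plural, and the Objectives and Discussion frame the associations across both groups. A reader might infer that the plan expressly rules out adjusting the group contrast. It does not; it names no adjusted between-group analysis. That narrower statement stands.
- **Ethnicity.** A reader might infer that the plan leaves ethnicity out despite treating it as a driver of the microbiome. The documents do not support this. The confounder list is open-ended. The remark that "cultural and dietary practices may influence these factors differently from Western populations" contrasts Malaysia with Western populations, not ethnic groups among these children.
- **Any imbalance would be read as an ASD effect.** This goes too far. An imbalance biases the contrast only if it also predicts the outcome. The planned socio-demographic comparison would make it visible, and many of the children come from the same town. Seeing an imbalance does not remove its effect, however, and the plan does not say how the result would be used.
- **Limitations are acknowledged.** The Discussion lists the observational design and convenience sampling, but offers no analytic remedy.
- **Detail left to a fuller plan.** A complete covariate list could well be left out of an article. Here the article names the between-group tests and attaches the adjustment elsewhere, so the point concerns what is stated.
- **Magnitude.** The percentages rest on assumed imbalances and a continuous outcome. They do not quantify error for beta diversity, for which this section names no specific test.

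**Conclusion.** The point holds in this form: the ASD-versus-TD comparisons are unadjusted as written, and the stated adjustment for SES belongs, by position and wording, to the regression among cases, where it cannot address confounding between clinic cases and convenience-sampled controls. Age is handled by matching, so the gap is mainly SES, with ethnicity a lesser and less certain part.

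The size is unknown from the documents. Under the assumptions shown (bias of 0.06 to 0.40 SD, continuous outcome, 30 or 40 per group), the false-positive rate runs from essentially nominal, 5.6%, to about 42%, against about 5% with SES as a covariate. The low end is as much part of the result as the high end. A reader might take 42% as the expected error rate; nothing in the documents supports that. The point should be fixed, because the contrast is central, the plan itself names the confounder and the data are being collected. It is not a fatal flaw.

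**What to change.** State that the primary ASD-versus-TD comparisons are group-plus-covariate models: linear, logistic or ordinal regression as the outcome requires, and PERMANOVA for beta diversity. Each should include:

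- group;
- age, as the matching factor;
- one prespecified SES measure, such as household income;
- ethnicity, with sparse categories collapsed, where numbers allow.

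Report the unadjusted results alongside. Keep diet for a secondary model, because it may lie on the pathway between ASD and the microbiota. Say explicitly that the age and SES adjustment applies to the group contrast as well as to the regression among cases.

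The cost is a few degrees of freedom out of at most 80 children, and possible sparse cells where the three-level SGNA ranking meets several ethnic categories; collapsing categories eases the second. No new data are needed. The wording should be settled before the group data are analysed; results are expected in December 2026.
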